#### Subgroup analyses

No sub-group analyses are planned other than those described above.

#### Frequency of analyses

The primary analysis will take place when follow-up is complete for all recruited patients. No formal interim analysis is planned. Given the nature of the intervention, we do not propose to have a formal Data Monitoring and Safety Committee (DMSC). We will report unexpected serious adverse events and deaths to the trial Sponsor. In these reports, the data will be presented by group but the allocation will remain masked, unless we are requested to disclose allocation because of concern about safety.

### Changes to the protocol since first approved

Substantial and minor amendments have been made. Inclusion and exclusion criteria have been amended to include a wider age range of patients and to facilitate recruitment. The primary outcome was changed from Troponin T to Troponin I because the coordinating centre measures Troponin I routinely. The type of blood sample collection was clarified in terms of distinguishing between serum and plasma concentrations. Anaesthetic details were removed to allow the operating team to follow their local practice. A more complete list of expected adverse events was added. Novel proteomic analyses on biopsies collected in a subgroup of participants have been added to characterise potential mechanistic pathways for RIPC. The sample size was increased by 25% to allow the proteomic analyses to be carried out in a subset of participants and to allow the trial to detect a smaller target difference between groups within each surgery stratum separately. The current version of the protocol is version 3 dated 17 July 2014.

### Measures to reduce the risk of bias

The trial has been designed to minimise the risk of bias. The trial is randomised, with stratification by centre and surgical stratum, so it is at low risk of allocation bias/confounding. Randomisation is unlikely to be subverted because random allocations are only issued after participants’ identity and eligibility are confirmed and securely documented. Blocked allocation could increase the risk of subversion bias, but this risk is being minimised by using varying block size. In order to subvert the trial, one person would need to know all allocations (across all surgeons) up to a particular timepoint; since different research nurses administer the intervention for different participants, this scenario would require collusion between research nurses.

The trial is at some risk of attrition bias because patients can decide to withdraw after randomisation or the care team could decide to withdraw them. However, we will try to minimise the probability of attrition bias by randomising the patient at a time close to the intervention. In addition, patients may not complete the follow-up questionnaire after discharge. We do not anticipate that attrition will be different between groups.

The trial is at low risk of ascertainment bias (outcome assessment) because the outcomes are objective and the analysts measuring blood or cellular markers are blinded to the allocation. Blinding of patients, the clinical care staff and the research team collecting the data, minimises risk of performance and detection biases. Success of blinding of patients will be assessed in the follow-up questionnaire.

Risk of bias in analysing the trial data is also low because analyses will be done according to a pre-specified statistical analysis plan and with an intention-to-treat basis.

### Dissemination of findings

The findings will be disseminated by usual academic channels, that is, presentation at international meetings, as well as by peer-reviewed publications and through patient organisations and newsletters to patients, where available. As the study compares surgical techniques no commercially exploitable findings are anticipated.

## Discussion

### What the study will investigate

We hypothesise that RIPC will reduce myocardial injury and reduce inflammation following heart surgery and that this effect will be greater in participants having AVR than in those having CABG. The effects of RIPC have been investigated in several trials to date, but their results have been inconsistent. By measuring many markers in myocardial biopsies and in blood samples, at different times after administering RIPC or sham RIPC, we expect to be able to relate changes in potential signalling mechanisms to the extent of myocardial injury measured by troponin I.

### Study design

The study design is a two-centre, randomised controlled trial with patients (CABG or valve) being randomly assigned to receive RIPC or control (sham RIPC) just before the surgery. This study design follows the one used in ERICCA [19]. Before this study commenced, we had discussions with the ERICCA trial team, and we tried to have our study as a sub-study to ERICCA. This was not possible because of the need for substantial protocol and governance changes, which were difficult to implement in a large ongoing multicentre study. Nevertheless, we adopted the same intervention and comparator. Our study population, however, is different; ERICCA is recruiting patients having CABG (with or without valve surgery) with an additive Euroscore greater than or equal to 5, whereas we have deliberately recruited patients undergoing CABG only or AVR only (regardless of their Euroscore). These differences in the trial populations meant that both centres taking part in this trial have also recruited to ERICCA at the same time.

### Challenges in study procedures

It has been suggested that some drugs interact with remote ischaemic preconditioning. Propofol and Fluorane, two of the most commonly used drugs in anaesthetic practice, are two such drugs. Propofol may inhibit STAT-5 transcription [51], hence reducing the preconditioning effect, while Fluorane may enhance protection [52]. However, there is a lack of firm evidence to substantiate these potential effects on the ischaemic preconditioning pathway. Therefore, for consistency, we have opted for the strategy of the ERICCA trial, which does not specify an anaesthetic protocol and allows each centre to follow its own practice. The two centres recruiting to this study adhere to their own, well-documented centre-specific protocols, minimizing variability in the anaesthetic procedures used between patients at the same centre. Stratified randomization ensures that patients allocated to both the intervention and control group within a centre will undergo the same anaesthetic procedures. Moreover, we will be able (albeit with low statistical power) to describe the interaction between centre and intervention.

Despite being a two-centre study, this study will recruit CABG patients at only one centre (ICHT). This is because the cardioplegia protocol for this operation differs between the two centres (warm blood versus cold blood), and it is believed that this might influence selected outcomes. This is hindering the recruitment rate, together with the challenges in recruiting patients to the AVR group in both centres because AVR operations are less frequent.

The intervention is carried out primarily in the anaesthetic room. Blinding of the operating team and carrying out the intervention can be challenging at this stage of the study because it coincides with the pre-operative anaesthetic procedures. The time a patient spends in the anaesthetic room can vary, and on some occasions the intervention can be incomplete by the time the patient is ready for theatre. To prevent delay of surgery, the intervention is completed in theatre as the patient is being prepared for surgery before sternotomy.

In order to monitor the changes in biomarker outcomes, blood samples are collected at various time points during a participant’s hospital stay. Some of these blood sample collections are scheduled outside office working hours. Even though reminders about the need to collect these samples are ‘handed over’ to the clinical team in charge of the patient when shifts change, on some occasions sample collection may be missed due to lack of time and other priorities. Similarly, there may be instances in which the biopsies are not collected; we aim to minimise this risk by having a member of the research team present in the theatre to prompt the operator to take the biopsies.

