### Statistical analyses

#### Plan of analysis

Continuous outcomes will be summarised and presented graphically as geometric means and standard errors, assuming that a natural logarithmic transformation will be applied to the data to normalise their distributions [50]. The primary outcome, Troponin-I, and the secondary outcomes such as markers of kinase activity, oxidative stress and inflammation, are all measured multiple times in each patient (see Table 1). Therefore, Troponin-I and the other markers will be analysed by fitting multilevel mixed effect linear regression models, which consider the repeated measures in an appropriate and efficient manner. These models will fit both fixed effects (intervention, surgical stratum, centre, time and the interactions of intervention x time and intervention x centre) and a random effect. The fixed effects are analogous to standard regression coefficients and are estimated directly. The random effect is not directly estimated but is summarized according to its estimated variances and covariance. Baseline (pre-intervention) measures, where available, will be analysed jointly with the post-intervention measure(s). The interaction of group and surgical stratum will be tested and, if statistically significant at the 10% level, the treatment effect will be reported for each stratum separately; otherwise, an overall treatment effect will be given. Similarly, interactions of group and time and group and centre, will be explored (overall or within stratum depending on the significance of the group by stratum interaction) and, if statistically significant at the 10% level, the treatment effect will be reported for each time point separately.

Analyses will be adjusted for stratification factors, namely surgical procedure and centre. Findings will be reported as effect sizes with 95% confidence intervals. Analyses will be based on the intention-to-treat; cross-overs are expected to be rare. The frequencies of complications and conversions will be tabulated descriptively, by pathology. However, the trial is not powered to detect differences in adverse events and no statistical comparisons will be carried out.

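### With CABG recruited at one centre only, the listed model and the group-by-centre rule let a pathology difference appear as a centre difference, and the model list does not match the planned stratum test

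*Protocol article*

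**What the plan says.** The Discussion of the protocol article (Challenges in study procedures) states that "this study will recruit CABG patients at only one centre (ICHT", because the cardioplegia protocol for CABG differs between the centres. It also mentions "challenges in recruiting patients to the AVR group in both centres", so AVR comes from ICHT and Bristol. The AVR split is not given. The same section says that anaesthesia follows each centre's own practice and that "we will be able (albeit with low statistical power) to describe the interaction between centre and intervention".

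The Plan of analysis lists the fixed effects as "intervention, surgical stratum, centre, time and the interactions of intervention x time and intervention x centre". Intervention by surgical stratum is not in this list. Later in the same paragraph: "The interaction of group and surgical stratum will be tested and, if statistically significant at the 10% level, the treatment effect will be reported for" (the strata are then shown apart; failing significance, one overall effect is given). Then "interactions of group and time and group and centre, will be explored", either overall or within stratum according to the result of the stratum test. Significance at 10% leads to a treatment effect for each time point.

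Objective 2 (Aims and objectives) is to test whether the RIPC effect differs between CABG and AVR. The Discussion hypothesises a larger effect in AVR. The Sample size section gives 30 per arm per stratum and 90% power for 0.43 SD overall, assuming no interaction with pathology. It does not mention a centre interaction.

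**The concern.** Bristol contributes AVR patients only, and ICHT contributes all the CABG patients plus some AVR patients. Comparing the RIPC effect between centres is therefore partly a comparison between pathologies. A model with intervention by centre but no intervention by stratum attributes a pathology difference to centre.

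The sequential rule allows the same thing. If the stratum test is not significant, centre is explored overall, so a real pathology difference that the test missed can reappear as a centre finding. A reader could then attribute it to local anaesthetic practice, which the Discussion names as a possible modifier.

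Two smaller faults go with this. If the stratum test is significant, the within-stratum exploration of centre is impossible for CABG. And reporting by time point is a sensible response to a group-by-time interaction, but it says nothing about how the centres differ.

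**Working it through.** **Inputs.** From Sample size: 30 per arm per stratum, pre-post correlation 0.3, post-post correlation 0.5. From Blood samples: five post-operative measures; one pre-intervention baseline is used. Assumed: two-sided 5% level for power (consistent with the planned 95% confidence intervals), and *b* AVR participants per arm at Bristol, varied from 5 to 25 because the split is not stated.

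**The plan's own figure.** Variance factor for the mean of five post measures adjusted for one baseline: f = (1 + 4×0.5)/5 − 0.3² = 0.60 − 0.09 = 0.51. With 60 per arm, SE = √(2×0.51/60) = 0.1304. Then 0.43/0.1304 = 3.30 and power = Φ(3.30 − 1.96) = 91%, against 90% stated, so the figure is reproduced. The within-stratum serum figure (0.55 SD, 30 per arm) gives 84.7% against 80% stated. That is on the safe side, and nothing below depends on it.

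**Mixing.** Let the true effect be 0 in CABG and δ in AVR, with no true centre difference. Per arm, ICHT has 30 CABG and 30 − b AVR; Bristol has b AVR. In the listed model the ICHT effect is δ(30 − b)/(60 − b) and the Bristol effect is δ. The apparent centre interaction is the difference, 30δ/(60 − b). At b = 15 this is 30/45 = 0.67δ; for δ = 0.55 SD it is 0.37 SD.

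**Overall effect if intervention by centre is kept.** Variance relative to the model without it:
- ICHT-reference coefficient: 60/(60 − b)
- equal centre weights: 900/[b(60 − b)]
- patient-share weights: 1

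At b = 15 the first two are both 1.333, so the SE is multiplied by 1.155, giving 0.151, and power for 0.43 SD is Φ(0.43/0.151 − 1.96), about 82%. Equal centre weights also shift the estimand: in the mixing example they give δ(45 − b)/(60 − b), or 0.67δ at b = 15, against 0.50δ over all participants.

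**Stratum interaction at the 10% level, true difference 0.55 SD.** Without intervention by centre: SE = √(2×0.51/30 + 2×0.51/30) = 0.261, power Φ(0.55/0.261 − 1.645) = 68%. With both interactions it rests on ICHT alone: SE = √(2×0.51/30 + 2×0.51/(30 − b)), which is 0.319 at b = 15, power 53%.

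| AVR at Bristol (2b) | Apparent centre interaction, share of δ | Power at 0.43 SD, ICHT reference | Equal centre weights | Patient-share weights | Stratum test power, both interactions fitted |
|---|---|---|---|---|---|
| 10 | 0.55 | 88% | 45% | 91% | 64% |
| 20 | 0.60 | 85% | 69% | 91% | 60% |
| 30 | 0.67 | 82% | 82% | 91% | 53% |
| 40 | 0.75 | 77% | 88% | 91% | 44% |
| 50 | 0.86 | 71% | 90% | 91% | 30% |

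**How often the fallback to the overall exploration occurs.** At a true difference of 0.55 SD the stratum test misses it with probability 1 − 0.68 = 32% when the centre interaction is left out, and 1 − 0.53 = 47% when it is fitted at a 30/30 split.

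**The reverse leak.** If the centre term is left out and centre truly modifies the effect by γ, the AVR effect takes up (b/30)γ: half of γ at b = 15, and one third to two thirds for 20 to 40 AVR participants at Bristol.

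**The case against.** The strongest reply is that the plan already covers most of this. The stratum interaction is missing only from the list in parentheses; the same paragraph tests it and makes reporting depend on it. If that test is significant, centre is explored within stratum, which in practice means within AVR, the clean comparison. This stands. A reader might infer from the list that objective 2 has no test, and the document does not support that. The reply does not cover a missed stratum difference, after which centre is explored overall.

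A reader might also infer that centre and pathology cannot be separated at all. That is not so. AVR is recruited at both centres, both main effects are fitted, and both interactions are estimable when fitted together. The stratum interaction then comes from ICHT alone, at lower precision. Recruiting CABG at one centre is a disclosed choice with a stated reason.

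A third tempting inference is that the overall effect necessarily loses power. The article does not say that intervention by centre is retained when the overall effect is reported, nor how centres would be weighted, and an article may leave contrast weights to the analysis plan. Patient-share weights, or dropping the term, cost nothing.

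Finally, the Sample size section claims no power for an interaction test, so the 68% and 53% contradict nothing stated. The article itself says there is no firm evidence of anaesthetic modification. Both points stand. The power figures serve only to show how often the fallback occurs.

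**Conclusion.** The point holds as an inconsistent model specification and a badly fixed exploration rule, not as an absent test or a confounded design. In the model as listed, or after a non-significant stratum test, a pure pathology difference appears as a centre interaction of 0.67 of its size at an assumed 30/30 AVR split (0.55 to 0.86 over 10 to 50 AVR participants at Bristol). Two faults need no assumption about the split: group by centre is inestimable within CABG, and reporting by time point does not describe a centre difference. The first biases nothing by itself.

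The fall in power for 0.43 SD from 91% to about 82% is conditional on a 30/30 split and on the ICHT-reference coefficient or equal centre weights. It should not be read as a property of the plan. The calculations assume equal arms within each cell, the correlations stated in the Sample size section and a two-sided 5% level for the overall effect. The matter should be corrected before analysis; it does not threaten the trial.

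**What to change.** In the Plan of analysis:
- Name intervention by stratum in the model, to match the test in the same paragraph.
- Take the overall effect from the model without intervention by centre.
- Estimate intervention by centre within AVR only, as an exploratory analysis, and report it by centre. Keep reporting by time point for the group-by-time interaction.
- Test the stratum interaction on all participants, and add a pre-specified sensitivity analysis comparing CABG with AVR at ICHT only. The first lets in part of any true centre modification; the second is free of it.

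In Challenges in study procedures, state that the centre interaction is described within AVR only.

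The cost is wording and one sensitivity analysis, with no change to recruitment or sample size. The centre interaction will rest on about 60 AVR participants. The ICHT-only check is less precise: its SE is 22% larger than that of the all-participant test at a 30/30 split, and 5% to 87% larger over the range examined.

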## Trial status

The trial opened for recruitment in one centre (ICHT) in February 2013 and in the other centre (UH Bristol) in June 2013. Recruitment is ongoing.

## Abbreviations

ADP: adenosine diphosphate
AMP: adenosine monophosphate
ATP: adenosine 5’ triphosphate
AVR: aortic valve replacement/repair
CABG: coronary artery bypass grafting
CPB: cardiopulmonary bypass
CRF: case report form
GFR: glomerular filtration rate
EIA: enzyme immunoassay
ELISA: enzyme-linked immunosorbent assay
Erk: extracellular signal-regulated kinases
IABP: intra-aortic ballon pump
ICHT: Imperial College Healthcare NHS Trust
ICU: intensive care unit
IL-6: interleukin-6
IL-8: interleukin-8
IL-10: interleukin-10
IMP: inosine 5’-monophosphate
JNK: c-Jun N-terminal kinases
MDA: malondialdehyde
MPTP: mitochondrial permeability transition pore
mRNA: messenger ribonucleic acid
NAD+: nicotinamide adenine dinucleotide
P38MAPK: P38 mitogen-activated protein kinases
PCI: percutaneous coronary intervention
PI3K: phosphoinositide 3-kinase inhibitor
PIS: patient information sheet
RIPC: remote ischaemic preconditioning
REC: research ethics committee
RISK: reperfusion injury salvage kinase
SAE: serious adverse event
STAT5: transcription 5
TNFαm: tumor factor necrosis α
UH Bristol: University Hospitals of Bristol NHS Foundation Trust
